#### Demographic information

Several demographics will be collected, including the patient’s age (categorised as ‘18–29’, ‘30–39’, ‘40–49’, 50–59’, ‘60+’), sex, education (five categories ranging from ‘primary education’ to ‘degree or postgraduate third-level education’) and ethnicity.

#### COVID-19 symptomatology

Patient experience of COVID-19 will be measured via a 13-item measure that assesses the presence, or absence, of COVID-19 symptoms. This measure consists of 12 commonly reported COVID-19 symptoms (fever, cough, shortness of breath or difficulty with breathing, headaches, aches and pains, fatigue/tiredness, nausea, diarrhoea, sore throat, loss of appetite, loss of taste and loss of smell) and an additional open-ended option for ‘other’. For each symptom, participants will be asked to indicate whether they experienced the symptom in the first 2 weeks following their diagnosis.

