Second, patient symptom profiles of COVID-19 and postacute COVID-19 will be identified using a quantitative method approach (objective 2). Identifying patient symptom profiles of COVID-19 and postacute COVID-19 may highlight potential subgroups of patients who may be more likely to present with higher symptomatology or different sets of co-occurring symptoms. In addition, predictors, such as demographic variables and pre-existing comorbidities, of the COVID-19 symptom profiles will be determined. Identifying these predictors may be of particular benefit to identifying patients who may need to be monitored for a longer duration. For example, identifying patients who are likely to remain symptomatic (particularly symptoms such as shortness of breath) may need to be monitored for a longer duration after acute COVID-19. Furthermore, identifying such profiles may aid COVID-19-positive patients in being prepared for a likely set of symptoms that they may experience long term, depending on the predictors of the COVID-19 symptom profiles. For example, identifying patients who are likely to have persistent symptoms such as fatigue and loss of taste/smell may be useful in helping the patient being prepared for these long-term effects.

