#### Postacute COVID-19 (long-COVID-19)

To assess for the presence, or absence, of postacute COVID-19 symptoms, patients will be presented with the same 13-item measure (fever, cough, shortness of breath or difficulty with breathing, headaches, aches and pains, fatigue/tiredness, nausea, diarrhoea, sore throat, loss of appetite, loss of taste, loss of smell and an additional open-ended option for ‘other’) as the COVID-19 symptomatology questionnaire. However, they will be asked to indicate whether they continued experiencing the symptom for more than 2 weeks following their diagnosis and/or are still currently experiencing the symptom.

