Third, latent classes, or symptom profiles, of COVID-19 and postacute COVID-19 will be examined through latent class analysis (LCA), using robust maximum likelihood estimation. To determine the optimal number of latent classes, models with one to six classes will be examined. To avoid solutions based on local maxima, 500 random sets of starting values will be used followed by 100 final stage optimisations. Several fit indices will be used to determine the fit of each latent class model, including the Akaike information criterion (AIC),^50^ the Bayesian information criterion (BIC),^51^ the sample size-adjusted BIC (ssaBIC),^52^ entropy values and the Lo-Mendell-Rubin-adjusted likelihood ratio test (LMR-A).^53^ Lower AIC, BIC and ssaBIC values and higher entropy values are indicative of better model fit. A non-significant LMR-A value suggests that the model with one less class should be accepted. In the event that an insufficient sample size is gathered, then a cluster analysis will be conducted instead.

Next, to determine the predictors of each symptom profile, a multinomial logistic regression will be performed by regressing the latent classes (identified during the class enumeration process) onto several covariates, using the R3STEP function in Mplus.^54 55^ This three-step procedure involves first identifying the most appropriate latent classes; then obtaining the most likely class memberships based on the posterior probabilities of the LCA, while accounting for the classification uncertainty rate (ie, measurement error) and, finally, the most likely class memberships are analysed with the covariates, thereby accounting for at least some of the misclassification errors.^55 56^

Fourth, the interviews will be transcribed verbatim. A thematic analysis will be conducted using NVivo V.12^57^ to identify common themes throughout the interviews. An inductive approach will be taken to draw out themes, without a pre-existing theory in the literature or based on the researchers’ preconceptions, by one researcher through familiarisation with the data, initial coding, refinement and subsequently grouped into themes to best represent the data. It will then be reviewed by the research team to ensure that all emerging topics are included and consensus is reached. A secondary researcher will independently code a subset of transcripts to assess the internal reliability.

### Measures: work package 2

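### If loss of taste and loss of smell stay associated within classes, the planned class selection can respond only by adding symptom profiles; residuals for this pair should be checked before a solution is accepted

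*Protocol article*

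**What the plan says.** In the Protocol article, the section on COVID-19 symptomatology describes a "13-item measure that assesses the presence, or absence, of COVID-19 symptoms". It has twelve named symptoms plus an open-ended other, and among the twelve are "sore throat, loss of appetite, loss of taste and loss of smell". The section on postacute COVID-19 uses the same list, again with two items: "loss of appetite, loss of taste, loss of smell and an additional open-ended option".

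Under Data analysis: work package 1, "latent classes, or symptom profiles, of COVID-19 and postacute COVID-19 will be examined through latent class analysis (LCA") with robust maximum likelihood, and "models with one to six classes will be examined". The number of classes is judged by AIC, BIC, ssaBIC, entropy and the adjusted Lo-Mendell-Rubin test (LMR-A). The chosen classes are then regressed on covariates with R3STEP. Cluster analysis replaces LCA if the sample is too small.

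The section does not mention local independence, residual association or merging of items. The Introduction, in describing objective 2, names the two symptoms together when it speaks of "persistent symptoms such as fatigue and loss of taste/smell".

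**The concern.** Standard LCA lets items be correlated overall but assumes that they are independent within each class. Loss of taste and loss of smell are closely related complaints, and some association may well remain after class membership is accounted for.

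The stated procedure offers only one response to such leftover association, which is another class. All five criteria compare or grade solutions with different numbers of classes; none asks whether the independence assumption holds in the chosen solution. R3STEP corrects for uncertain class membership, not for a wrong number of classes.

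An existing profile could therefore be reported twice, once with and once without taste and smell loss, and the two versions then regressed on predictors. The Introduction intends the profiles to inform who may need longer monitoring and what patients are told to expect, so such a split would be interpreted.

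**Working it through.** **Inputs from the article.** Twelve binary named symptoms; one to six classes; 925 discharged patients as the ceiling on N; no response rate. There is no planned sample size or error rate for the LCA, so there is no figure to reproduce. The within-class taste–smell association is not given and is varied below as an assumption.

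**Why N matters.** With 12 binary items, a K-class model has (K − 1) + 12K = 13K − 1 parameters, so BIC = −2 lnL + (13K − 1) ln N. One more class costs 13 ln N:
- N = 150: 13 × 5.01 = 65.1
- N = 300: 13 × 5.70 = 74.2
- N = 925: 13 × 6.83 = 88.8

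From N = 150 to 925 this penalty grows 1.36-fold (88.8/65.1). The log-likelihood gain from explaining a fixed leftover association grows in proportion to N, 6.2-fold (925/150). BIC therefore resists in small samples and gives way in larger ones.

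**BIC, two assumed true classes (50/50).** Replicates out of 25 in which BIC chose more than two classes, by within-class phi between the two items (classes 1 to 4 fitted):

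| N | phi 0 | 0.2 | 0.4 | 0.6 | 0.8 |
|---|---|---|---|---|---|
| 150 | 0 | 0 | 0 | 3 | 22 |
| 300 | 0 | 0 | 1 | 19 | 25 |
| 925 | 0 | 0 | 18 | 25 | 25 |

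With the pair merged into one item, BIC chose two classes in 25/25 in every cell.

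**ssaBIC, three assumed true classes.** Share of 24 replicates choosing more than three classes, separate items v merged, by within-class tetrachoric correlation rho (classes 1 to 6 fitted):

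| N | rho 0 | 0.5 | 0.8 |
|---|---|---|---|
| 200 | 38% v 33% | 54% v 25% | 100% v 33% |
| 300 | 12% v 12% | 67% v 8% | 100% v 4% |
| 450 | 8% v 0% | 71% v 4% | 100% v 0% |

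The two scales connect, at 50% prevalence, through phi = (2/π) arcsin(rho): rho 0.5 gives 0.33 and rho 0.8 gives 0.59. In this design BIC exceeded three classes in 0%, 4% and 29% at rho 0.8. AIC did so in 96–100% at rho 0.5 for N of 300 and 450, but also about half the time with no dependence.

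**Sensitivity to the design.** A three-class design with 200 datasets per cell at rho 0.8 had BIC choosing four or more classes in 10%, 39% and 91% at N = 200, 300 and 450, and ssaBIC choosing five or six in 95–98%. After merging, BIC was right in 97–100% and ssaBIC in 67%, 91% and 98%. A further three-class design (16 replicates per cell, rho 0.5 to 0.8, N of 200 to 400) had ssaBIC choosing too many in 81–100% with separate items and 0–38% merged. There BIC did so in 0% of replicates, except 50% at rho 0.8 and N = 400.

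**What the extra classes are.** In eight replicates per cell of the two-class design, classes 1 to 6 were fitted and the two most similar classes of the chosen solution compared. At N = 300 with phi 0.8, and at N = 925 with phi 0.6 or 0.8, their item probabilities differed on average by 0.04–0.07 on the other ten items and by 0.78–0.91 on taste and smell. At weaker dependence (N = 300, phi 0.6; N = 925, phi 0.4) the picture was mixed: 0.17–0.19 against 0.61–0.78, averages that include some two-class solutions.

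**Precision.** With 16 to 25 replicates, the standard error of a share near 50% is 10 to 12.5 percentage points (for example √(0.25/25) = 0.10).

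**The case against.** A reader might infer that listing the two symptoms separately in itself breaks local independence and will produce false profiles. The article does not support that. The assumption fails only if association remains within classes, and no figure for this is given. At phi of 0.2 or less BIC added no class at any N tested, and at phi 0.4 it did so in 0/25 and 1/25 at N = 150 and 300. The achieved N is also unknown: N = 300 would need a response of 32% (300/925).

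Nor is a class marked by taste and smell loss necessarily an artefact. The Introduction gives persistent loss of this kind as an example of what objective 2 looks for. A combined item still lets such a profile emerge; it only stops the pair being counted twice.

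It can also fairly be said that the article never fixes the exact indicator set, that a journal article commonly leaves residual diagnostics to a fuller plan, and that their absence is not an error. That stands. Part of the over-extraction by AIC, and by ssaBIC at N = 200, occurs without any dependence and cannot be charged to this pair. Entropy and LMR-A were not simulated, so the final choice under all five criteria is not known.

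What remains is narrower. The article sets out its selection procedure in detail, and every stated criterion concerns the number of classes. Leftover association would therefore be handled in the one way that alters the result.

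**Conclusion.** The point holds in conditional form. If loss of taste and loss of smell remain associated within classes, the stated procedure can favour extra profiles that, under strong dependence, differ almost only on this pair, and it would carry them into R3STEP. Over an assumed within-class tetrachoric correlation of 0 to 0.8, the excess attributable to the pair runs from about none to near-certain over-extraction by ssaBIC. For BIC it runs from none to frequent, depending on N and on how well separated the true classes are.

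This rests on assumed class structures, assumed associations and modest numbers of replicates. It does not show that the reported profiles will be wrong, and nothing printed in the article is false. It is a worthwhile and inexpensive improvement, held with medium confidence.

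**What to change.** In both the acute and the postacute LCA, inspect bivariate residuals before accepting a solution. Where the taste–smell residual is large, either free the within-class association between the two items or replace them with one indicator for loss of taste, smell or both, which leaves 11 indicators. Report whether the number and content of the profiles change, and do so before interpreting any class that differs only on this pair. Keep the separate items in the descriptive tables.

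The cost is some added wording and a little more analysis; data collection is unchanged. If the items are merged, profiles that differ in taste loss versus smell loss can no longer be separated. Freeing the association avoids that loss at the price of extra parameters.

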### Participants and recruitment strategy

Participants will consist of patients and healthcare staff recruited from the clinic site. First, patients who have completed their treatment via remote monitoring will be recruited to gather information on their experiences of the intervention in the form of a quantitative survey. Patient recruitment will begin in February 2021 and end in June 2021. A total of 925 patients have been discharged from the remote monitoring service. Patients will be recruited via an email sent through gatekeepers at the clinic site. All patients will receive an email with the participant information sheet and a link to an online survey. A subsample of these patients will also be recruited for a qualitative interview regarding their experiences of remote monitoring. As part of the survey, patients have the option of indicating if they wish to participate in a telephone interview and provide their contact details. Patients who consented to interview will be purposively sampled to get a representative sample based on age, gender and education. These patients will then be contacted by a member of the research team to arrange a suitable time for interview, once 7 days have passed since signing the consent form.

Second, staff who have been remotely monitoring patients with COVID-19 will be recruited via an email sent through gatekeepers at the clinic site. These participants will begin to be recruited in February 2021 and end in June 2021. A total of 25 staff worked in the virtual clinic since it was set up in April 2020. All staff who worked in the clinic will receive an invitation to participate in a qualitative interview regarding their experiences of remote monitoring from a healthcare staff perspective. If they choose to take part, a member of the research team will contact them to schedule a suitable time for a telephone interview, once 7 days have passed since signing the consent form.

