### Ethics and dissemination

Ethical approval has been granted by the National Research Ethics Committee for COVID-19-related Research (NREC COVID-19; reference number: 20-NREC-COV-093). Data sharing agreements have been put in place between the University College Dublin (UCD) research team and the hospital. The data will be deidentified and securely transferred to the research team, in accordance with data protection regulations. No identifiable data will be included in the data set received by the research team at UCD. Online consent will be obtained from the participants of this project.

Findings will be disseminated via publications in scientific journals, policy briefs, short reports and social media. A summary of the findings will also be shared with participants who informed the research team that they are interested in the results of the project.

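### Acute symptoms are asked about only from diagnosis, up to about 14 months later, and no listed measure records when diagnosis was, so symptom profiles can partly reflect test delay and recall lag

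*Protocol article*

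**What the plan says.** *Participants and recruitment strategy* fixes the calendar. On the clinic: "A total of 25 staff worked in the virtual clinic since it was set up in April 2020". On the survey: "Patient recruitment will begin in February 2021 and end in June 2021". The sampling frame is the whole discharged group: "A total of 925 patients have been discharged from the remote monitoring service", and "All patients will receive an email with the participant information sheet and a link to an online survey". The inclusion and exclusion criteria set no limit on time since diagnosis or discharge.

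*COVID-19 symptomatology* defines the acute item, which covers 12 named symptoms and an open option: "participants will be asked to indicate whether they experienced the symptom in the first 2 weeks following their diagnosis". *Postacute COVID-19 (long-COVID-19)* repeats the list and asks whether the patient "continued experiencing the symptom for more than 2 weeks following their diagnosis and/or are still currently experiencing the symptom". Both windows are anchored to diagnosis. No symptom item covers the time between onset and diagnosis.

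The other patient measures are demographics, comorbidities, app experience, user acceptance, adherence and patient–professional interaction. None, as listed, is a date of diagnosis, test or onset.

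*Data analysis: work package 1* uses the symptom items as indicators in latent class analysis (LCA), then regresses the classes on unnamed covariates with R3STEP. The Introduction names demographics and comorbidities as examples of predictors. The stated limitations cover generalisability and temporal ordering, but not recall or variable time since diagnosis.

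**The concern.** Two features of measurement enter the LCA indicators, and neither is a feature of the illness.

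The first is where the window opens. The article's own Introduction describes an early viral phase followed by an inflammatory one. A window that opens at diagnosis samples different parts of that course according to how late the patient was tested. A fever that came and went before the test is recorded as no fever.

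The second is elapsed time. Patients answer the same question at very different distances from the event. If reporting fades, long-lag patients look less symptomatic.

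The aim is to find profiles and predictors that indicate who may need longer monitoring and what patients should expect. Class membership is the outcome of the predictor regression, so a covariate that happens to be associated with date of infection or test delay could pick up a measurement effect. R3STEP allows for uncertainty in class assignment given the indicators. It does not correct indicators whose meaning shifts with lag.

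**Working it through.** **Recall interval.** The article gives no figure, so this is calendar arithmetic on its dates (days divided by 30.4375).

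- Longest: 1 April 2020 to 30 June 2021 is 455 days, or 14.95 months.
- An April 2020 patient answering in June 2021: at least 397 days (30 April to 1 June), or 13.0 months. By month count, April to June of the next year is 14.
- An April 2020 patient answering in February 2021: 277 to 333 days, or 9.1 to 10.9 months.
- Shortest: not derivable. A recently discharged patient could answer within weeks.

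**Window.** Acute item: from diagnosis to 2 weeks after. Post-acute item: beyond 2 weeks after diagnosis, or current. A symptom that started and ended before diagnosis meets neither, so under literal reading it is scored absent on both.

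**Does elapsed time also distort the post-acute item through recovery?** The two limbs are joined by and/or. A symptom that has continued and is still present more than 2 weeks after diagnosis already satisfies the first limb. Assuming, for illustration, exponential persistence with a median of 60 days, the item is truly positive in 0.5^(14/60) = 0.85 of those with the symptom, whether they are surveyed at 1, 3 or 12 months. What remains for this item is recall.

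**Possible size.** This is a simulation in which every input is assumed. There are 12 binary items and two true classes of 50% each, with item probabilities of 0.50 to 0.95 in the high class and 0.12 to 0.65 in the low class. Lag is uniform over 0 to 14 months and test delay uniform over 0 to 10 days. The reporting probability is

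p(class, item) × (1 − r × lag/14) × (1 − t × delay/10),

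with the last factor applied to six symptoms treated as early. A two-class model was fitted, with 25 runs per setting. The table gives the mean probability of being placed in the high-symptom class; the true value is 0.50 in every group.

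| Assumed loss | Groups compared | n = 300 | n = 925 |
|---|---|---|---|
| none | lag under 4 v over 10 months | 0.50 v 0.49 | 0.50 v 0.51 |
| r = 10% | same | 0.54 v 0.49 | 0.53 v 0.47 |
| r = 30% | same | 0.55 v 0.36 | 0.55 v 0.39 |
| r = 50% | same | 0.56 v 0.25 | 0.57 v 0.25 |
| none | delay under 3 v over 7 days | 0.49 v 0.50 | 0.51 v 0.51 |
| t = 30% | same | 0.53 v 0.45 | 0.53 v 0.45 |
| t = 50% | same | 0.55 v 0.42 | 0.54 v 0.42 |

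The size n = 925 would need every discharged patient to respond; n = 300 is an arbitrary smaller sample.

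**Does it create false classes?** With a single true class and the same mechanisms, the BIC preferred two classes in none of 60 runs in every setting but one (n = 925, t = 80%), where it did so in 2 of 60 (3%). The effect falls on who is placed in which profile and on profile prevalence, much less on the number of profiles.

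**The case against.** The strongest reply is that this is partly an argument from silence in a condensed article. The demographics are introduced by "Several demographics will be collected, including the" and are not a closed list, the R3STEP covariates are not named, and the questionnaire is not shown. That stands as far as the date is concerned: the most that can be said is that no listed measure records it. It does not touch the acute window. That wording is stated, and a date held elsewhere would not recover symptoms that were never asked about.

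A reader might infer from "No identifiable data will be included in the data set received by the research team at UCD" that time since diagnosis is lost for good. The article does not support that. It describes data sharing agreements and a de-identified transfer from the hospital without saying what is transferred, and month and year of a test is not in itself identifying.

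A reader might also infer that the post-acute item drifts with recovery over the year. As shown in the working, the and/or wording largely prevents this.

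Third, it can be said that diagnosis is a dated event common to all patients, whereas onset is itself recalled and gives windows of unequal length. That is a fair cost of the rewording. It has to be weighed against an item that systematically drops pre-test symptoms.

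Finally, the larger shifts in the simulation need 30% to 50% loss. At 10% the gap is only 0.04 to 0.06 beyond chance differences of about 0.01. The article gives no recall or test-delay figure with which to choose between these.

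**Conclusion.** The point holds in a limited form. Three things are established from the text: a look-back of up to about 14 months with no eligibility limit on lag, an acute window that omits anything resolved before diagnosis, and no listed measure of when diagnosis or onset occurred. It follows that class membership and its predictors can partly reflect test delay and recall lag. That they will do so, or by how much, does not follow. The size depends on recall loss and the spread of test delay, neither of which the article gives.

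Two stronger readings should be resisted. One is that a low-symptom class would simply be a class of patients diagnosed long ago; in the simulation these mechanisms almost never produced a spurious class. The other is that age and comorbidity effects are confounded with epidemic wave. That also needs lag or test delay to be associated with age or comorbidity, and the article says nothing on this.

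This is a worthwhile improvement at low cost. It does not invalidate objective 2.

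**What to change.** 1. Reword the acute item to run from first symptoms until 2 weeks after diagnosis.
2. Record month and year of the positive test, as one survey item or as a non-identifying field in the hospital transfer. If the date is already held, say so. The survey item is simpler because it needs no linkage.
3. Report the distribution of time since diagnosis, and enter it as a covariate in the R3STEP regressions for both the acute and the post-acute profiles.
4. Add recall and variable time since diagnosis to the stated limitations.
5. Optionally, if the sample allows, repeat the LCAs in respondents within 6 months of diagnosis. The article already foresees that the sample may be too small for LCA, so this should not be mandatory.

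The costs are slight respondent burden, an onset that is itself recalled, an acute window whose length differs between patients, and one extra parameter per class contrast (at most 6 − 1 = 5 per model if six classes were chosen and lag enters linearly). The covariate adjusts the predictor estimates for lag. It does not repair the indicators, so the rewording and the limitation are still needed. The wording can be changed only before the survey is answered; the date might still be obtained afterwards.
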